#### Visit 6 (1st Follow-up visit)

Applicable to all study patients. 15 days (+/-2 days) after the last IMP administration, a follow-up visit will take place. Investigator will assess occurrence of any on-going or new AEs. AEs will be followed until final outcome as described in Section 7.4.

- Concomitant Medication
- Adverse Events
- Vital Signs
- Blood sample for assessment WBC and differential for monitoring of neutrophils granulocytes
- Urine analysis RNA
- Proteomics
- Urine analysis dip slide and bacterial culture
- Blood sample (RNA)
- Flow Cytometry urine sample
- ACSS

Safety telephone call at day 30

Applicable to all study patients.

- Concomitant Medication
- Adverse Events
- ACSS

Visit 7 (Final Visit)

Applicable to all study patients in week 26 (+/5 days). In addition patient premature withdrawn from the study will, if possible and if patient agrees, have the procedures and assessments performed according to this final visit.

- Urine pregnancy test
- Concomitant Medication
- Physical Examination
- Adverse Events
- Vital Signs
- Blood Samples for assessment WBC and differential for monitoring of neutrophils granulocytes
- Urine analysis RNA
- Proteomics

- Urine analysis dip slide and bacterial culture
- Blood sample (RNA)
- Flow Cytometry urine sample
- ACSS

### Unscheduled Visits

During the treatment period patients treated with Kineret® or Nitrofurantoin Uro-Tablinen® will be advised to contact the investigating site in case of signs and symptoms of recurrent acute cystitis infection or any side effects. An Unscheduled visit will, at the discretion of the investigator, be scheduled. Assessments performed at this visit will be:

- Concomitant medication
- Adverse Events
- Vital Signs
- Blood sample (haematology and biochemistry)
- Urine analysis RNA
- Proteomics
- Urine analysis dip slide and bacterial culture
- Blood sample (RNA)
- Flow Cytometry urine sample
- ACSS

Patients are encouraged to report to the study center as soon as they feel symptoms of cystitis in order to record symptoms with the ACSS.

According to symptoms additional assessment may take place, at the discretion of the investigator. The visit will be documented in the Unscheduled Visit Form in the eCRF.

In addition, during the follow-up period, the patients will be advised to contact the investigating site in case of signs and symptoms of recurrent acute cystitis infection or side effects. An Unscheduled Visit will, at the discretion of the investigator, be scheduled. Assessments performed at this visit will be the same as for the study treatment visits. According to signs and symptoms additional assessment may take place, at the discretion of the investigator. The visit will be documented in the Unscheduled Visit Form in the eCRF.

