### 3.1 Objectives

#### 3.1.1 Primary Efficacy Objective

To investigate treatment efficacy of Kineret compared to Nitrofurantoin in female patients with an acute episode of recurrent cystitis.

- a) To investigate whether Kineret is effective in treatment of acute cystitis.
- b) To investigate whether Kineret treatment decreases the incidence of recurrent cystitis.

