#### 3.2.3 Secondary Endpoints

- a) Presence of bacteriuria at each visit up to week 26 of study
- b) Presence of leucocyturia at each visit up to week 26 of study
- c) Recurrent UTI episodes up to 6 months
- d) Urine proteomics
- e) Gene expression analysis
- f) DNA sequence analysis

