## 4 Trial Design

### 4.1 Overall Trial Design

**Figure 1: Course of the trial**

The duration of conventional treatment of acute cystitis with antibiotics is one to five days, depending on the antibiotic substance. The follow up period of 26 weeks is chosen to analyse frequency of recurrent cystitis.

[figure not shown]

This will be a single center, randomized, open-labeled clinical trial in female subjects with a history of recurrent acute cystitis. The subjects will be randomised to receive either 5 days of Kineret treatment, 100 mg daily as a subcutaneous injection through daily visits at the study clinic or Nitrofurantoin oral antibiotic treatment for 5 days.

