#### Visits 2 and 5 Treatment Visits

Applicable to study patients of both treatment arms.

- Concomitant Medication
- Dispensing of Kineret®
- Adverse Events
- Vital Signs
- Blood sample (haematology and biochemistry)
- Urine analysis (RNA)
- Proteomics
- Urine analysis dip slide and bacterial culture
- Blood sample (RNA)
- Flow Cytometry urine sample
- ACSS (only on visit 5)

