### Early Termination Visit

Patients are free to discontinue their participation in the trial at any time and for whatever reason without affecting their right to further treatment and to an appropriate follow-up investigation. As described in section 5.6, patients may also be discontinued from the trial at any time at the discretion of the Investigator. The date and reason for withdrawal of a patient or premature discontinuation of the trial must be documented in the eCRF and the patient's medical record. The monitor should be notified if a patient discontinues prematurely from the trial.

Patient premature withdrawn from the study will, if possible and if patient agrees, have the procedures and assessments performed according to the final visit as described above.

Patients that will develop treatment failure in either arms will be treated with alternative, antibiogram directed antibiotics, and not withdrawn from study.

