## ACSS-Fragebogen

## Kontrollvorstellung (Folgebefund) – Teil B

Uhrzeit: \_\_\_\_ UU: \_\_\_\_ MM Datum der Untersuchung: \_\_\_\_ / \_\_\_\_ / \_\_\_\_ (Tag/Monat/Jahr)

Bitte geben Sie an, ob Sie irgendwelche Änderungen in Ihrem Zustand seit dem Ausfüllen des ersten Teils unseres Fragebogens bemerkt haben? (kreuzen Sie bitte Ihre Antwort an):

- Dynamik**
- ☐ 0 Ich fühle mich jetzt ausgezeichnet (alle Symptome sind endgültig vergangen)
- ☐ 1 Mir geht es jetzt wesentlich besser (die Mehrheit der Symptome sind vergangen)
- ☐ 2 Ich fühle mich jetzt nur gering besser (die Mehrheit der Symptome sind immer noch da)
- ☐ 3 Es gibt jetzt keine Änderung meines Zustands (alle Symptome sind noch vorhanden)
- ☐ 4 Es ist jetzt schlimmer geworden (mein Zustand hat sich verschlechtert)

Bitte geben Sie an, ob Sie unten genannte Symptome innerhalb der letzten 24 Stunden bemerkt haben, und bewerten Sie bitte deren Intensität (nur eine Antwort für jedes einzelne Symptom):

|                                   |                                                                                                                                                                                                                                                                           | 0                                                                                                                                                                                                                                                                                                                                                                                                                           | 1                                                                               | 2                                                                        | 3                                                                |

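### Cystitis episodes that arise and resolve between the Day 30 call and week 26 (152 of 182 days) have no assured route into the data, so capture of recurrences can differ by arm.

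*Protocol*

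**What the plan says.** Section 3.1.1 gives part (b) of the primary efficacy objective as "To investigate whether Kineret treatment decreases the incidence of recurrent cystitis". Section 3.2.3 carries it as a secondary endpoint, "Recurrent UTI episodes up to 6 months", and Section 4.1 states why follow-up is as long as it is: "The follow up period of 26 weeks is chosen to analyse frequency of recurrent cystitis". The trial is open label.

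After treatment, Sections 6.1 and 6.2 schedule three contacts for all patients: Visit 6 (ACSS and culture), the Day 30 telephone call (ACSS) and Visit 7 at week 26 ± 5 days (ACSS and culture). Between them, patients are advised to contact the site if they have symptoms. The Unscheduled Visits text says for the treatment period "An Unscheduled visit will, at the discretion of the investigator, be scheduled" and repeats the sentence for follow-up. It adds for follow-up: "Assessments performed at this visit will be the same as for the study treatment visits".

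The ACSS Part B symptom items in Section 22.3 ask what the patient has noticed in the last 24 hours ("innerhalb der letzten 24 Stunden bemerkt haben"). Section 7.1 requires adverse events to be recorded up to 30 days after the last dose. Section 6.7 has the investigator ask about medication at every contact, but one of its sentences limits eCRF recording to the period from randomisation to the last dose of study drug.

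**The concern.** A recurrence that starts and settles within the long unscheduled stretch reaches the database only if two voluntary steps occur: the patient contacts the site, and an unblinded investigator acts on the contact. Nothing listed at Visit 7 is designed to recover an episode missed at either step.

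Both steps can depend on treatment. The patient knows whether she had an antibiotic or an injection, and so does the investigator. If readiness to call, or to be called in, differs by arm, the comparison of recurrence partly measures who was seen. With 20 and 10 patients, one patient wrongly counted as recurrence-free moves the Kineret proportion by 5 points (1/20) or the Nitrofurantoin proportion by 10 points (1/10). What is at stake is part (b) of the primary objective and the purpose of the follow-up.

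**Working it through.** **Length of the gap.** The inputs are the Day 30 call and Visit 7 at week 26 ± 5 days (Section 6.1); 26 × 7 = 182 days.

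- Nominal: (182 − 30)/182 = 152/182 = 83.5%.
- Visit 7 at its earliest: (177 − 30)/177 = 147/177 = 83.1%.
- Visit 7 at its latest: (187 − 30)/187 = 157/187 = 84.0%.
- Counted from the end of treatment on Day 5: 152/177 = 85.9%.

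The chart and the text place Visit 6 differently (Day 15, or 15 days after the last dose). Both fall before Day 30, so the gap does not change. The protocol states no expected recurrence rate or power for recurrence, so there is no figure of its own to reproduce.

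**Routes by which an episode inside the gap could be recorded.**

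- *Unscheduled visit:* needs the patient to make contact, then the investigator's discretion.
- *ACSS at Visit 7:* the symptom and quality-of-life items cover 24 hours. The opening Part B item compares her state with the first form, but its answers describe how she feels now.
- *History at Visit 7:* none listed. Medical history is taken only at Visit 1.
- *Adverse events:* Visit 7 lists them, but the required window closes at Day 5 + 30 = Day 35, which covers 5 of the 152 days.
- *Concomitant medication:* Visit 7 lists it and Section 6.7 requires the question. Within that section, one sentence ends eCRF recording at the last study dose, while another requires concomitant treatment in the medical record and eCRF with indication and dates and sets no time limit. The two are not reconciled, so an antibiotic course given elsewhere in month 4 may or may not be entered.

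No route is assured.

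**What unequal capture could do.** The documents give no capture rates, so every value here is an assumption. Observed proportion = true proportion × capture.

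| True Kineret / Nitrofurantoin | Capture Kineret / Nitrofurantoin | Observed | Difference |
|---|---|---|---|
| 50% / 50% | equal, 100% | 50% / 50% | 0 |
| 50% / 50% | 90% / 75% | 45% / 37.5% | +7.5 points |
| 50% / 50% | 90% / 60% | 45% / 30% | +15 points |
| 50% / 50% | 60% / 90% | 30% / 45% | −15 points |
| 30% / 60% | 90% / 45% | 27% / 27% | 0 (true −30) |
| 30% / 60% | 60% / 90% | 18% / 54% | −36 (true −30) |

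The error can create, hide or enlarge a difference. The table shows that either direction is possible; it does not predict one.

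**The case against.** The opposing case has substance, and it limits the point.

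- *Recurrences are found only when patients volunteer them.* A reader might infer this, but the schedule does not support it. Visit 6, the Day 30 call and Visit 7 apply the ACSS to everyone, with culture at Visits 6 and 7. An episode present then is found without a call and without discretion. Early reporting is also encouraged, and medication is asked about at each contact. The weakness is confined to episodes that arise and resolve in the gap.
- *Persistence is counted as recurrence, or non-resolution as zero recurrences.* The treatment-period text speaks of recurrent symptoms, and Section 6.2 keeps failures in the study: "Patients that will develop treatment failure in either arms will be treated with alternative, antibiogram directed antibiotics, and not withdrawn from study". A reader might join the two. But the first is advice on when to call, failure is named separately, and no counting rule is stated. Such a rule belongs in the SAP, which is not shown, and keeping failures in follow-up preserves data.
- *Follow-up unscheduled visits omit the ACSS.* The text points to the treatment visits, where Visits 2 and 5 list it as "ACSS (only on visit 5" and closed bracket, and Visits 3 and 4 not at all. Yet the unscheduled column of the chart includes the ACSS, and the same section encourages reporting so that it can be completed. This is loose wording to tidy, not a firm contradiction.
- *The trial is a pilot and recurrence is a secondary endpoint.* True, but recurrence also appears in the primary objective.

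The objection that the SAP may settle the matter does not stand for the core. An SAP can define a recurrence; it cannot supply an episode, score or culture that was never recorded.

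**Conclusion.** The point holds for episodes that arise and resolve between Day 30 and week 26: 152 of 182 days, 83.5% (83.1% to 84.0% across the visit window). For these, recording depends on patient initiative and on the discretion of an investigator who knows the arm, and no listed procedure reliably recovers what is missed. Differential capture is therefore possible for an outcome named in the primary objective.

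The size and direction of any bias cannot be stated. The documents give no capture rates, and if capture were equal in both arms the proportions would be understated without a spurious difference under no effect. Projecting the entry criterion's past episode rates onto treated patients would not give a sound count of episodes at risk. The correction is worth making because it is cheap and can only be made while data are being collected.

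**What to change.** 1. In the follow-up part of Unscheduled Visits, require every report of cystitis symptoms to be logged in the eCRF in both arms, whether or not the patient is seen. Offer the unscheduled-visit ACSS and culture by the same rule in both arms instead of at discretion.
2. At the Day 30 call and Visit 7, ask all patients one fixed question: any urinary tract infection or antibiotic course since the last contact, with date, treatment and where treated. State that the answer goes into the eCRF notwithstanding the recording limits in Sections 6.7 and 7.1.
3. Reword the follow-up sentence on unscheduled assessments to match the unscheduled column of the Section 6.1 chart, which includes the ACSS.

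The cost is an amendment, a symptom-report log and one eCRF question at two existing contacts. Expect a few more unscheduled visits among 30 patients, using assessments already planned. Recall over about five months at Visit 7 will be imperfect; logging reports as they come in reduces that but does not remove it.

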### Early Termination Visit

Patients are free to discontinue their participation in the trial at any time and for whatever reason without affecting their right to further treatment and to an appropriate follow-up investigation. As described in section 5.6, patients may also be discontinued from the trial at any time at the discretion of the Investigator. The date and reason for withdrawal of a patient or premature discontinuation of the trial must be documented in the eCRF and the patient's medical record. The monitor should be notified if a patient discontinues prematurely from the trial.

Patient premature withdrawn from the study will, if possible and if patient agrees, have the procedures and assessments performed according to the final visit as described above.

Patients that will develop treatment failure in either arms will be treated with alternative, antibiogram directed antibiotics, and not withdrawn from study.

### 6.3 Demographics

Demographic data will comprise of:

- Year of birth
- Gender
- Ethnicity/ Race

### 6.4 Vital Signs

Vital signs (resting blood pressure and heart rate) must be assessed.

Recording of vital signs comprises:

- Heart rate (beats per minute), supine after 5 min rest
- Blood pressure, systolic and diastolic (mmHg), supine after 5 min rest
- Body temperature
- Height
- Weight

The same arm will be used for all measurements. The arm (right or left) used for measurement will be recorded in the CRF.

Assessment of vital signs resulting in abnormal values will be repeated in order to exclude an erroneous assessment. Individual results will be classified as “normal”, “abnormal of no clinical significance” or “abnormal of clinical significance”.

## **6.5 Physical Examination**

A general physical examination should be performed.

## **6.6 Medical History and Concurrent Medical Conditions**

Significant medical history (specified in 6.1) within the last 12 months incl. medical history of recurrent cystitis and all concurrent medical conditions must be obtained at the screening visit.

## **6.7 Concomitant Medication**

At each study visit/contact, the investigator should question the subject about any medication taken by the subject.

All concomitant medication, with the exception of vitamins and/or dietary supplements, administered during the time period from randomisation to last administration of study drug, are to be recorded in the eCRF. This also applies to concomitant medication administered prophylactically in anticipation of reaction to the active treatment and any medication intended to treat an AE.

A prophylactic medication is a medication administered in the absence of ANY symptom and in anticipation of a reaction to the active treatment (e.g. an anti-pyretic, corticosteroids, etc.).

Similarly, concomitant medication administered for the treatment of a SAE at any time, must be recorded on the SAE Report as applicable.

Use of non-marketed/other investigational products one month prior to Visit 1 and during the trial is not permitted.

Refer to Appendix 2 for the definition of a SAE and to Section 7.7 for the applicable reporting periods and required information.

Use of concomitant treatment must be recorded in the subject's medical record and the eCRF detailing treatment/drug name, dose, indication and dates of start and stop.

## 6.8 Pregnancy Test

A urine pregnancy test must be performed at the trial site at Visit 1 (before study treatment) and Visit 7 in female subjects of childbearing potential.

## 6.9 Adverse Events

Adverse events must be assessed and recorded as specified in section 7.

## 6.10 Laboratory Assessments

### 6.10.1 Safety Blood Tests (hematology, biochemistry)

Samples for analysis of parameters must be taken according to the schedule of trial procedures (section 6.1) or on withdrawal from or early completion of the treatment phase of the clinical trial.

| The following analyses will be performed on the venipunctured blood samples: | Parameter                                                                                                                                                                 |
|------------------------------------------------------------------------------|---------------------------------------------------------------------------------------------------------------------------------------------------------------------------|
| Haematology                                                                  | Haemoglobin
Haematocrit
Red blood cell (RBC) count
Mean corpuscular volume (MCV)
White blood cell (WBC) count, including differential count
Platelet count |
| Biochemistry (serum/plasma)                                                  | Urea
Creatinine
Sodium
Potassium
Glucose                                                                                                                      |

If any laboratory results are abnormal, the investigator should follow-up the subject as clinically appropriate.

Routine analyses of blood samples (clinical chemistry) will be processed at the central laboratory of the university hospital Giessen-Marburg, location Giessen. At the end of the clinical trial, parts of the samples are shipped to the local laboratory at the Lund University, Sweden. Handling and shipment instructions are provided in laboratory manuals by the laboratory at the Lund University.

### 6.10.2 Safety Urine analysis

Samples for analysis of the parameters listed below must be taken as specified in the schedule of trial procedures (section 6.1) or on withdrawal from or early completion of the treatment phase of the clinical trial.

| The following analyses will be performed on the mid-stream urine samples: | Parameter                                                                                                                     |
|---------------------------------------------------------------------------|-------------------------------------------------------------------------------------------------------------------------------|
| Urine analysis                                                            | Bacterial culture

Leucocyte counts in uncentrifuged urine by flow cytometry

Dip slide for hematuria, leucocytes |

Routine analyses of urine samples (microbiology) will be processed at the microbiology laboratory of the Clinic and Polyclinic for Urology, Pediatric Urology and Andrology, Giessen. Urine status analysis (leucocyte counts) will be carried out at the central laboratory of the university hospital Giessen-Marburg, location Giessen. Urine dip stick tests (urine analysis) and urine culture analyses will be carried out at the laboratory of the Clinic and Polyclinic for Urology, Pediatric Urology and Andrology, Giessen. At the end of the clinical trial, parts of the samples are shipped to the laboratory at the Lund University, Sweden.

### 6.10.3 Urine Samples for efficacy

| Analyses       | Parameter                                                                                                                     |
|----------------|-------------------------------------------------------------------------------------------------------------------------------|
| Urine analysis | Bacterial culture

Leucocyte counts in uncentrifuged urine by flow cytometry

Dip slide for hematuria, leucocytes |

Prior to and after treatment, urine samples will be obtained and analyzed.

Routine analyses of urine samples (microbiology) will be processed at the microbiology laboratory of the Clinic and Polyclinic for Urology, Pediatric Urology and Andrology, Giessen. Urine status analysis (leucocyte counts) will be carried out at the central laboratory of the university hospital Giessen-Marburg, location Giessen. Urine dip stick tests (urine analysis) and urine culture analyses will be carried out laboratory of the Clinic and Polyclinic for Urology, Pediatric Urology and Andrology, Giessen. At the end of the clinical trial, parts of the samples are shipped to the laboratory at the Lund University, Sweden.

